# Sample size

The aim of our trial is to study whether high intense physical exercise reduces burden of AF more than low intense physical exercise. Our primary outcome, burden of AF, is assessed as total number of ECGs with AF. We expect to reduce the burden of AF with 25%. The patients send an ECG twice daily and in case of symptoms which will sum up to 300 ECG per patient. We assume that total number of ECGs with AF in the low intense group will be 20 compared to 15 in the high intense group. The estimated power will be 94.3% for α=0.05 (two-sided 95% CI) and SD=6, which is higher than the generally accepted power of 80%.

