# Methods

The study is an assessor blinded, randomized controlled trial. Patients are randomized by simple drawing. For logistic reasons, an exercise team consists of ten patients. The letters A and B are equally distributed in 20 envelopes, and represents the physical exercise intensity. The sealed envelopes are all put into a larger envelope from where the patients will draw one envelope at randomization.

[figure not shown]
A total of 60 patients with paroxysmal/persistent AF will be included, using consecutive sampling, from the Department of Cardiology, Copenhagen University Hospital Hvidovre. After inclusion, baseline tests will be performed as follows: physical capacity measured on Six Minute Walk Test and maximal physical capacity measured on ergometer bike, Figure 1. Patient characteristics, medication, risk factors and comorbidity will be registered. Before the exercise intervention, all participants will complete a nurse-led rehabilitation program regarding AF. The patients will then be randomized to either low intensity physical exercise (50% of maximum physical exertion) or high intensity physical exercise (75-85% of maximum physical exertion).

The exercise intervention lasts 12 weeks with exercise sessions twice weekly of 60 and 90 minutes duration, respectively. They consist of cardiovascular exercise (cycling, running) and will be supervised by cardiac physiotherapists. Intensity is measured as perceived exertion on Borg 20 scale introduced at the initial sessions. The exercise sessions will be conducted at the hospital.

During the intervention and two months after the last exercise session, the patients upload an electrocardiogram (ECG) from a handheld ECG-device twice daily and in case of symptoms of AF.

One year after the intervention is completed the patients will be invited to a follow-up. During the follow-up time all hospital admissions are registered from the medical records.

At baseline and after the 12-week intervention, blood samples will be taken and stored in a bio bank for later analyses. A total of 90 mL. blood per participant will be drawn. The blood samples will be stored anonymously at minus 80 degrees Celsius for 10 years for future research.

The trial is expected to start in October 2012 with end of follow-up one year after the last exercise session.

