# Statistical analyses

Patient characteristics and baseline data will be analyzed using descriptive statistics. Parametric data will be reported as mean and standard deviation (SD), non-parametric data as median and range. Depending on the distribution, student-t-test or non-parametric tests will be used when comparing the intervention groups.

The effect of exercise will be analyzed in several ways depending on outcome variable; burden of AF and hospital admissions are analyzed by Poisson regression analysis, survival analyses (time-to-event) using Kaplan-Meier plots and hazard regression analysis. All analyses will be adjusted for common cardiac comorbidities and reported with two-sided confidence intervals. A p-value < 0.05 is considered statistically significant.

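### The 94.3% power is labelled two-sided but matches a one-sided calculation; 60 patients give about 89% at two-sided α = 0.05

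*Protocol*

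**What the plan says.** The Sample size section of the protocol defines the primary outcome as the number of ECGs with AF per patient and assumes that the mean "in the low intense group will be 20 compared to 15 in the high intense group", a 25% reduction. It then states: "The estimated power will be 94.3% for α=0.05 (two-sided 95% CI) and SD=6". It compares this with a benchmark of 80%. It does not give the number of patients, the test or the formula.

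The number comes from Methods: "A total of 60 patients with paroxysmal/persistent AF will be included". Allocation is balanced ("The letters A and B are equally distributed in 20 envelopes"), which gives 30 per arm.

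The Statistical analyses section is also two-sided. Results are to be "reported with two-sided confidence intervals. A p-value < 0.05 is considered statistically significant".

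**The concern.** The power sentence labels its α as two-sided, and the analysis section agrees. The stated means, SD and sample size nevertheless give a clearly lower power at two-sided 0.05, and the printed value coincides with the one-sided result.

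This is the protocol's only power statement and its only quantitative support for 60 patients. If the figure is one-sided, the margin over 80% is about 9 to 10 points rather than 14. No allowance for patients who cannot be analysed is stated, so that margin is all there is to absorb losses.

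**Working it through.** **Inputs**

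- Means 20 and 15, difference 5 (Sample size)
- SD 6 (Sample size)
- α = 0.05, two-sided (Sample size; Statistical analyses)
- 60 patients in total, equal allocation, so n = 30 per arm (Methods)

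**Standardised difference**

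SE = SD × √(2/n) = 6 × √(2/30) = 1.549

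δ = 5 / 1.549 = 3.227

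**Reproducing the printed figure**

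One-sided α = 0.05, normal approximation: Φ(3.227 − 1.645) = Φ(1.582) = 94.32%. This rounds to the printed 94.3%. The one-sided t-test gives 93.88%.

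**Power at the stated two-sided α**

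- Normal approximation: Φ(3.227 − 1.960) = Φ(1.267) = 89.75%
- t-test (noncentral t, 58 df, noncentrality 3.227): 88.76%

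The printed figure is too high by 94.3 − 89.75 = 4.5 points or 94.3 − 88.76 = 5.5 points. That is more than rounding or the choice between z and t can explain.

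**Risk of missing the assumed effect**

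- Implied by the protocol: 100 − 94.3 = 5.7%
- Two-sided, normal: 100 − 89.75 = 10.25%, about 1.8 times as large
- Two-sided, t-test: 100 − 88.76 = 11.24%, about 2.0 times as large

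**Could other readings give 94.3% two-sided?**

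- *More patients.* By the normal approximation 36 per arm gives 94.24%; by the t-test 37 per arm gives 94.25%. That means about 72 to 74 patients, against 60 planned.
- *Smaller SD.* With 30 per arm, the SD would have to be 5.47 (normal) or 5.38 (t-test) instead of 6.
- *Unequal split of 60.* This only lowers power; for example, 25 and 35 gives 87.9% by the t-test.
- *Rank test.* At a relative efficiency of 0.955, power is 87.3%.
- *Poisson rate ratio without overdispersion.* ln(20/15) / √(1/600 + 1/450) = 0.2877 / 0.0624 = 4.61, and Φ(4.61 − 1.96) = 99.6%.

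None of these variants gives 94.3% with 60 patients and the stated inputs.

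**How much margin is left**

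The protocol gives no loss rate, so these are illustrative assumptions (two-sided t-test):

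| Assumed loss | n per arm | Power |
|---|---|---|
| none | 30 | 88.8% |
| 10% | 27 | 85.2% |
| 20% | 24 | 80.7% |

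Sidedness also matters for the 20% reduction in the protocol's Hypotheses section. With 20 against 16, the same SD and 30 per arm, δ = 4 / 1.549 = 2.582. One-sided normal power is Φ(2.582 − 1.645) = 82.6%. Two-sided power is Φ(2.582 − 1.960) = 73.3%, or 71.9% by the t-test. For that effect, the one-sided figure lies above the 80% benchmark and the two-sided figure below it.

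**The case against.** The strongest reply is that nothing in the design turns on the error. The protocol uses the figure only to say that power exceeds 80%, and that remains true at 88.8 to 89.8%, and even at an assumed 20% loss. This stands, and it is why no change to the sample size is asked for. It does not make the printed number right.

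The one-sided origin is an inference, since the protocol names no formula or test. That also stands. But the mismatch with the two-sided inputs is there whatever its cause.

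Comparing a normal-approximation 94.3% with a t-test 88.8% mixes methods. Like for like, the drop is from 94.3% to 89.75%, and the miss risk rises about 1.8-fold. Both versions are shown for that reason, and 89 to 90% is the fair range.

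Finally, the planned analysis of AF burden is Poisson regression adjusted for comorbidities, so a t-test power is not the power of the primary analysis. This is correct, but the protocol's own figure rests on two means and an SD, so it is fairly checked on that basis. The corrected sentence should say that it is an approximation.

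**Conclusion.** The concern holds. With means of 20 and 15, SD 6, 30 analysable patients per arm and two-sided α = 0.05, power is 88.8% (t-test) or 89.8% (normal approximation), not 94.3%. The printed figure equals the one-sided normal-approximation value and contradicts both its own label and the two-sided analysis plan.

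The result takes the protocol's means and SD as given, uses the total from Methods with equal allocation, and assumes no losses. Power for the assumed 25% reduction stays above 80%, so the claim of adequate power survives with a smaller margin. The stated power itself is wrong and needs correcting.

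**What to change.** Replace the power sentence in the Sample size section with wording such as: *With 30 analysable patients per arm, means of 20 and 15 ECGs with AF and an SD of 6, a two-sided comparison of two means at α = 0.05 has about 89% power (t-test; 90% by the normal approximation). This approximates the planned Poisson analysis.*

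If the sponsor wishes to show the effect of losses, it can add that power would be about 85% with 10% loss and about 81% with 20% loss, stating that these rates are assumptions.

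Keep the total at 60. Relabelling the figure as one-sided would not do, because the analysis section commits to two-sided inference. The cost is one corrected sentence and a less favourable number, with no extra patients and no change to the design.

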# Side effects and risks

Drawing a blood sample can be painful and inconvenient when penetrating the skin and cause redness, local hematoma or infection. The electrodes used for 24-hour measurement of heart rate can cause inconvenience, itchiness or redness of the skin. Physical exercise can feel uncomfortably at high intensities. Testing maximal physical activity on ergometer bike is physically demanding and can induce discomfort, chest pain, dizziness or dyspnea in case of undiscovered cardiac disease. The test is conducted with continuous monitoring on ECG and observation of the patient by trained medical personal. Echocardiography is based on ultrasound waves, which is not associated with any short or long term risk. Handheld ECG-recording is not associated with any risk.

# Ethical considerations

Establishing a database with personal information and storing biological material is considered reasonable for the use in research.

Physical exercise is associated with several health benefits among healthy people and we find no evidence for a detrimental effect among patients with AF. Physical exercise can cause sore muscles or distortions of joint, which we try to prevent by thorough instruction and observation by physiotherapists. We expect that the patients will benefit by participating in this trial. Structured physical exercise, handheld recording of heart rhythm and nurse led education about AF is not part of standard care for patients with AF. This trial will contribute with important new research in a proper way regarding treatment of AF and guidance in physical exercise. We consider the health benefits of physical exercise to outweigh the potential risks.

Personal information will be handled in accordance with the national laws. Any new research based on this trial, which is not described in the above, has to be approved by The National Ethical Committee and the patients will be requested a new informed consent.

This protocol is written in accordance with the Helsinki Declaration. Informed consent has to be signed at inclusion to the study and covers both the participation in the exercise intervention as well as permission to store biological material. Participation is voluntary and the participant can withdraw consent at any time. Whether the patient participates in the trial does not influence on the treatment otherwise which is emphasized in the written information of the trial and in the consent.

The participants are protected in accordance with the Law of Health and the Law of Storing Personal Information. Personal safety, rights and wellbeing are beyond any scientific or societal interests. All results no matter outcome will be published in relevant medical journals and released to the public media.

We have no declarations or conflicting interests.

